#### Pilot phase

The initial month of step one will serve as a pilot phase (see Fig. 2) and focus on evaluating the implementation strategy and address any major unforeseen challenges. Interviews with HCPs from cluster one will be conducted, and the research group will discuss any relevant changes with the advisory board. No changes will be made to the 15-method itself or the allocated time for the training sessions.

#### Process evaluation

A process evaluation will be conducted following the MRCs guideline on evaluating complex interventions [55]. Interviews will be conducted in active practices once during step one (with cluster one), and once during step two (with cluster one and two). Interviews will include practice owner(s) and staff to ensure multilevel evaluation. The interviews will include a minimum of 20 HCP in both individual interviews and focus groups and will have a duration of thirty to sixty minutes. Data collection will be guided by the Consolidated Framework for Implementation Research (CFIR) [56]. The evaluation will seek to identify barriers and facilitators of implementation, adoption of the 15-method, and context elements impacting implementation outcomes [31, 57]. Reporting on any potential adaptations and modifications to the 15-method during the study will be done by The Framework for Reporting on Adaptations and Modifications to Evidence-based interventions (FRAME) [58]. Further, the interviews will be used to assess potential adverse events, unintended trial effects, intervention adherence, and trial conduct.

The evaluation will further assess fidelity to the 15-method in three ways. First, the interviews conducted via the CFIR interview guide include assessment of the implementation process and use of the intervention. Second, the HCP will be offered feedback on their conversational skills via audio recordings. If the HCP choose to, they can record consultations for upload to a secure server on which the conversations will be coded by [name] who is an experienced Motivational Interviewing Treatment Integrity (MITI) [59] coder and a member of the Motivational Interviewing Network of Trainers (MINT). The HCP will then receive feedback on the conversation and the collected data can be used as complementary fidelity assessment. Third, assessment of the use of the intervention will be evaluated through an electronic patient questionnaire on tablets in a small subset of randomly selected practices. Patients who just exited from a consultation will be asked to fill in a two-item questionnaire, stating whether the HCP inquired about alcohol habits in today’s consultation. The collected data will help qualify outcome measure three, i.e. the likelihood of alcohol use being addressed during a consultation in general practice.

### Data collection

#### Frequency of alcohol related consultations in the practices

The HCPs will register any consultation in which the topic of alcohol is raised using the International Classification of Disease tenth revision (ICD-10) code Z00.6 (Encounter for examination for normal comparison and control in clinical research program) [60] as secondary diagnosis to the consultations main diagnosis. In the case of no primary diagnosis to the consultation, the HCPs will use the International Classification of Primary Care 2 (ICPC-2) code A97 (no disease) [61, 62] together with the ICD-10 Z00.6 code. The HCPs will use the codes from start of baseline and throughout the study period. Any consultation in which alcohol consumption and/or alcohol-related problems is addressed will count as an observation regardless of whether the 15-method has been used.

Further, data on smoking, exercise, alcohol, and weight will be collected along with the total number of face-to-face consultations (including video consultations) in the practices from baseline to end of study. Local registration codes are available, among others, on smoking status (daily, occasionally, quit, never), exercise (hours per week), alcohol intake (standard units per week), and weight in all Danish general practices [63, 64].

Data will be collected on practice level only. A data quality assessment will be conducted during step two (Fig. 1) in a sub-sample of practices.

#### Questionnaire data on alcohol consumption, quality of life, and lifestyle

To measure the proportion of patients exceeding the Danish low-risk alcohol consumption limits a questionnaire will be sent to all patients ≥ 18 years affiliated to the participating general practices four times during the study period. The questionnaire will be sent by e-Boks [65] which is the official, digital communication route between public authorities and Danish citizens. The e-Boks system is accessed by the two-phased password system NemId/MitID [66], which is linked to the personal social security number of all residents in Denmark. A form ensuring informed consent from the participant will be attached to the questionnaire. To participate, and provide informed consent, the participant must press a link embedded in the form. The participant is informed that pressing the link will constitute as informed consent and the participant will be directed to the questionnaire. Questionnaire data will be stored via the secure Research Electronic Data Capture (REDCap) database [67] provided by Open Patient data Explorative Network (OPEN) [68]. Non-responders will receive a reminder after 7–10 days.

The questionnaire is adapted from the TAP-study [27] and the Relay-study [69] and assesses:

1. Alcohol consumption by (i) three questions on consumption from the Alcohol Use Disorder Identification Test (AUDIT-C) [44, 70], and (ii) daily alcohol intake within the last week by The Timeline Follow Back (TLFB) [71] one-week version. The TLFB one-week version has been successfully applied online and through questionnaires [72–74] and the AUDIT-C is validated in primary care [75].

2. Smoking, nutrition and exercise habits.

3. Health related quality of life by the EuroQol 5D (EQ-5D) questionnaire [76] which is validated worldwide [77, 78].

4. Current subjective mental well-being by the World Health Organization Five-Well-Being Index (WHO-5), also validated worldwide [79].

5. Whether the patient has attempted to change any aspect of their lifestyle (smoking, exercise, alcohol, diet) within the last year.

The questionnaire is designed to assess lifestyle and health related quality of life in general and to avoid a focus entirely on alcohol use. Alcohol use disorders are associated with potential stigmatization [11, 22], and to avoid response bias the questions on alcohol are embedded in questions about diet, physical activity, smoking, and mental well-being and formulated in a non-offending manner.

One standard unit of alcohol is defined as 12 g of pure alcohol.

#### Pharmacological treatment and biomarkers

This will include prescriptions of Disulfiram, Naltrexone, Acamprosate and Nalmefene. Data on prescriptions will be collected from the Danish National Prescription Registry [80]. Data on the use of biomarkers will include Gamma-Glutamyltransferase (GGT) and Alanine-Aminotransferase (ALAT) and will be collected via the National Laboratory Database. Data will be collected on practice level.

#### Patient evaluations

Patient experiences with the 15-method will be evaluated in a qualitative follow-up study. We will recruit patients through HCPs who have used the 15-method in collaboration with their patients.

#### Data management, monitoring, and confidentiality

Data will be stored on secured servers provided by OPEN [68] which is part of the data infrastructure in The Region of Southern Denmark. Questionnaire data will be collected using the REDCap database [67] provided by and stored at OPEN. Data management and monitoring will be provided via OPEN data managers. The research team will conduct regular quality control of the data in collaboration with OPEN data managers and have full access to the final trial dataset. No data monitoring committee will be established as (i) no risk to the participants is expected, and (ii) data will be anonymized and analyzed on population or clinic level. Data will be stored at OPEN servers after the study is concluded and can be transferred to The Danish National Archive for long term storage if deemed relevant.

### Procedures

#### Power and sample size calculation

We hypothesize that the implementation of the 15-method can lead to a 10% reduction in the proportion of patients exceeding the Danish low-risk alcohol consumption limits of ten standard units per week and a maximum of 4 standard units per drinking day for women and men, in the practices participating in the study. In the Region of Southern Denmark, the proportion of adults exceeding the national alcohol consumption limits is 14.2% [81]. We further hypothesize that the implementation of the 15-method will increase the proportion of consultations in which the topic of alcohol is addressed from 5.3 to 9.8% [82] in the participating practices.

Calculations follow power and sample size calculations in stepped wedge cluster randomized trials [83, 84], resulting in a total of 16 general practices being randomized to the 15-method in four steps of four practices (clusters). A power calculation was conducted for each of the two objectives, i.e., lowering the proportion of patients exceeding the low-risk alcohol consumption limit, and increasing the likelihood of alcohol use being addressed during a consultation. Sample size estimates were based on the most conservative result of the two. We expected an average of 1538 patients per GP in the region [85], 2.3 GPs per practice [85], 89% of patients within the targeted age-group (≥ 18 years) per general practice [86], and an estimated response rate in the patient questionnaires of 50% [87–89]. To detect the difference between the proportions 14.2% and 12.8% (10% reduction) using an exact binomial test of proportions with a 2.5% significance level and with an expected intraclass correlation coefficient of 0.068 [90], an estimated power of > 90% was obtained.

With a total of 16 general practices, a power of 81% can be achieved with a patient questionnaire response rate of 37%.

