**Fig. 2 Fig2:**
[figure not shown]
Timeline of the Identification and Treatment of Alcohol Problems in Primary Care (iTAPP) Study. Stepped wedge cluster randomized controlled trial design with general practices in The Region of Southern Denmark

HCPs will register consultations in which alcohol is addressed from the start of the baseline period and throughout the study period (described below). Patient questionnaires will be sent four times during the study period; once during baseline, twice during implementation, and once at the end of the follow-up period.

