### Trial status spring 2024

As of March 2024, the iTAPP study includes eighteen practices. The first three clusters are active and use the 15-method in their everyday practice. The process evaluation is underway and currently concluding its data collection phase. Three of the four patient questionnaires have been distributed and yielded an average response rate of 30%. Three practices from the Danish feasibility study of the 15-method in primary care have continued as participants in the iTAPP study. As these three practices were familiar with the 15-method prior to the iTAPP study they are not included among the eighteen practices and data analyses will be kept separate.

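### The power stated for the first objective (>90% at 50% response, 81% at 37%) does not cover the 30% response the article reports; scaled from its own figures it is about 77% with eighteen practices

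*Protocol article*

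**What the plan says.** In the protocol article, the section Power and sample size calculation starts from "the proportion of adults exceeding the national alcohol consumption limits is 14.2"% and plans to detect a fall to 12.8%, "using an exact binomial test of proportions with a 2.5% significance level", "with an expected intraclass correlation coefficient of 0.068". Sidedness is not given. With 16 practices and "an estimated response rate in the patient questionnaires of 50"%, power is put above 90%. One less favourable case follows: "With a total of 16 general practices, a power of 81% can be achieved with a patient questionnaire response rate of 37"%.

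Under Timeline, the questionnaires are "sent four times during the study period; once during baseline, twice during implementation, and once at the end of the follow-up period".

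Trial status spring 2024 then reports eighteen practices, three launch groups active, and: "Three of the four patient questionnaires have been distributed and yielded an average response rate of 30"%. Methodological considerations adds that some patients are expected not to answer later rounds. None of these sections gives the power at the response obtained.

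**The concern.** The 37% case is the least favourable one the article plans for, and the article itself reports a lower response. A reader who takes the sample size section at face value would credit the first objective with 81% to over 90% power for a 10% relative reduction, although the condition attached to even the lower figure has not been met.

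This objective comes first in the aims, and the Discussion links evidence that the method reduces consumption to national roll-out. How much weight a non-significant result can bear depends on the chance of missing the planned effect. That chance is below 10% in the main planning case and 19% in the fallback. The question is what it is at 30% response with eighteen practices.

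**Working it through.** **Inputs, all from the protocol article.** Patients per GP 1538, GPs per practice 2.3, share aged 18 or over 89%, proportions 14.2% and 12.8% (an exact 10% reduction is 12.78%), level 2.5%, ICC 0.068, 16 practices planned and 18 reported, response 50% and 37% planned and 30% reported.

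**Respondents per wave.** Adults per practice: 1538 × 2.3 × 0.89 = 3148.
- 16 practices, 50%: 25,186
- 16 practices, 37%: 18,638 (the 81% case)
- 16 practices, 30%: 15,112
- 18 practices, 30%: 17,001

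The extra practices leave the trial about 9% short of the 81% case (17,001/18,638 = 0.91). For the four-wave average to reach 37%, the last wave would need 4 × 37 − 3 × 30 = 58%. To match the 81% case's respondent total with 18 practices it would need 4 × 37 × 16/18 − 90 = about 42%.

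**Reproducing the stated pair.** Two different calculations do so.

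1. Two proportions, eight practices' respondents per arm, no clustering term, one-sided 2.5%, p2 = 12.78%. Power = Φ(δ/SE − 1.960), with SE = √{[0.142 × 0.858 + 0.1278 × 0.8722]/n}.
   - 50%: n = 12,593, SE = 0.004304, δ/SE = 3.299, power 91.0%.
   - 37%: n = 9,319, SE = 0.005004, δ/SE = 2.838, power 81.0%.
2. Stepped-wedge design effect with three steps, one baseline and one measurement per step, ICC 0.068, two-sided 2.5%. The design effect is about 0.837; power is 91.4% and 80.5%.

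The stated method therefore cannot be identified from the two figures.

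**Rescaling the stated 81%.** In this step δ/SE is taken to grow with the square root of the number of respondents.
- Two-sided: 2.241 + 0.878 = 3.119 at 37%. Times √(30/37) = 2.809, and Φ(2.809 − 2.241) = 71.5%. Times √(18/16) = 2.979, and Φ(0.738) = 77.0%.
- One-sided: 1.960 + 0.878 = 2.838. The same steps give 2.555 (72.4%) and 2.710 (77.3%).

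So about 72% with 16 practices and 77% with 18, whichever sidedness was meant.

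**Four-wave stepped-wedge model.** Hussey-Hughes model with fixed wave effects and a random practice effect. The variance of a practice mean at one wave is σ²(1 − ρ)/m + ρσ², with ρ = 0.068, m = 3148 × response and σ² = p̄(1 − p̄). Four launch groups of equal size; waves at baseline, in two of steps 1 to 3, and at end of follow-up. Ranges cover the choice of steps and p2 = 12.8% or 12.78%.

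| Power, % | 50%, 16 practices | 37%, 16 | 30%, 16 | 30%, 18 |
|---|---|---|---|---|
| Stated | >90 | 81 | not given | not given |
| Stated 81% rescaled | – | 81 | 71.5–72.4 | 77.0–77.3 |
| Calculation 1, one-sided | 91.0 | 81.0 | 72.4 | 77.4 |
| Calculation 2, two-sided | 91.4 | 80.5 | 70.9 | 76.5 |
| Four-wave model, two-sided | 87.0–90.0 | 74.5–78.6 | 64.4–68.8 | 70.1–74.4 |
| Four-wave model, one-sided | 92.1–94.1 | 82.6–85.8 | 74.2–78.0 | 79.1–82.6 |

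With p2 = 12.8% alone, the last column is 70.1–73.0 two-sided and 79.1–81.5 one-sided.

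**Reduction detectable with 80% power, 18 practices, 30% response.**
- Rescaled, two-sided: 10% × (2.241 + 0.842)/2.979 = 10.3% relative.
- Four-wave model, SE about 0.00490 to 0.00506: two-sided, 3.083 × SE/0.142 = 10.6–11.0%; one-sided, 2.802 × SE/0.142 = 9.7–10.0%.

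**The case against.** **The quoted sentence is conditional and correct.** It says what 37% would deliver and claims nothing about 30%. The status section discloses both the 30% and the larger number of practices. This stands: the fault is a power statement left unrevised, not an arithmetic error.

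**The loss is modest.** On the article's own scaling the chance of missing the effect is 23%, against 19% in its fallback, and the detectable reduction moves little. That is fair against the fallback, less so against the headline figure above 90%. No passage says that a null result would be read as evidence of no effect; that risk lies with the reader.

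**A one-sided 2.5% level rescues the 81%.** With 18 practices the four-wave model then gives about 79–83%, which brackets it. This also stands, and it is why sidedness must be stated. The same model would have given 92–94% at 50%, so the headline figure is still not reached.

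**Wave dates and correlations are unknown.** The dates are in a figure not shown. Trial status helps, because three waves were out while only three launch groups were active, so the middle waves were very probably before step 4. Correlations cut both ways. At 30%, 16 practices and two-sided testing, the four-wave model gives 64–67% (p2 = 12.8%). A within-person correlation of 0.5 from repeat responders would raise this to 93–94%; a between-wave practice correlation of 0.99 instead of 1 would lower it to 41–43%. The documents give neither value, so the results hold on the plan's stated assumptions only.

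**Stronger readings that are not supported.** A reader might infer that the stated figures arise only if three equal steps are assumed, or that they flatter a four-group, four-survey design. The first fails because the unclustered one-sided calculation reproduces both figures. The second fails because, on a one-sided level, the four-wave model meets or exceeds both. A reader might also quote 64% as the trial's power; that is a 16-practice, two-sided figure, and the trial reports eighteen practices.

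**Conclusion.** The point holds as a needed restatement. The reported 30% response lies below both planning cases, and eighteen practices do not restore the respondent count behind the 81%. Scaled from the article's own figure, power for the 10% reduction is about 77% with 18 practices (72% had there been 16). The four-wave model with ICC 0.068 and 18 practices gives about 70–74% two-sided and 79–83% one-sided.

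These values rest on four assumptions: the average practice size used in planning also applies to the eighteen practices; the fourth wave responds like the first three; respondents are independent across waves; and there is no practice-by-wave variance. The four-wave figures also rest on the assumed wave timing and an even split of practices over launch groups. On these assumptions the figure above 90% is not delivered on any variant tried, and the 81% is reached only on the most favourable one-sided variants. The documents do not support a claim that the original calculation was wrong.

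**What to change.** Keep the planning calculation as a record, and add the power for the first objective at the observed response, eighteen practices and the actual four-wave exposure schedule, updated once the fourth wave is in. Give the relative reduction detectable with 80% power alongside it. State whether the 2.5% level is one- or two-sided, how the ICC entered the calculation, and what was assumed about repeat responders and practice-by-wave variance.

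The cost is a short recalculation and a few sentences. Design, recruitment and analysis are unchanged; the stated power will probably be less favourable.

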#### Recruitment and allocation

A computer-generated random sample of one hundred practices in The Region of Southern Denmark will be sent a letter of invitation to participate in the study. Non-responders will receive a follow-up phone call. Practices who show interest in participating will receive a formal visits or phone call to inform on the study. Practices owners will receive a written consent form including a contract with The University of Southern Denmark to be signed before enrolment. The recruitment procedure can be repeated if necessary.

Practices will be allocated to clusters based on a computer-generated random number sequence. As blinding to the intervention is not possible, information on the allocation sequence, i.e., which cluster the practice will belong to, will be distributed simultaneously to all practices via e-mail.

#### Test of patient questionnaire

The research group comprised a draft patient questionnaire from three validated questionnaires (AUDIT-C, EQ-5D, WHO-5), an alcohol consumption measure (TLFB one week version) and questions on smoking, nutrition, exercise, and efforts regarding habit change. The research group evaluated the content validity of the comprised questionnaire together with healthcare professionals and researchers from the Unit for Clinical Alcohol Research. Based on the feedback, the research group edited the draft and invited a second group to evaluate the updated version in a qualitative pilot test following the COSMIN checklist [91]. The second test group consisted of researchers from The Research Unit of General Practice Odense with expertise in questionnaire development, questionnaire-based research and patient reported outcome measures. Evaluations from the pilot testing were used to finalize the patient questionnaire.

### Analysis plan

#### Quantitative analyses

Analyses will be conducted by intention-to-treat principle [92]. Binary outcomes will be analyzed using mixed model logistic regression. Continuous outcomes, e.g., number of heavy drinking days, the use of biomarkers, and pharmacological prescription frequency will be analyzed using mixed model linear regression. Outcomes will be analyzed on practice level with weighted observations according to patient population size and number of participating HCPs in the practice [93].

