### Study setting

The iTAPP study is a collaborative study between The Unit for Clinical Alcohol Research at the Research Unit of Psychiatry Odense and The Research Unit of General Practice, Department of Public Health, The University of Southern Denmark.

The study will be conducted in general practices in the Region of Southern Denmark. All citizens with residence in Denmark are eligible for listing with a general practice, and 99% of Danish residents are affiliated with a GP [39, 40]. Consultation and treatment in general practice are free of charge. On average, all Danish citizens are in contact with their GP approximately seven times a year [41] and the GP is often the first point of contact to the health care system, as referral to e.g. office-based specialists and in- and outpatient hospitals occur through the GP in most cases. The GP is thus both first-line provider and gatekeeper to the secondary health care system [41]. Denmark has approximately 3500 GPs in 1650 practice units. The Region of Southern Denmark holds approximately 345 practice units [42] with an average of 2.3 GPs and 1,541 patients per GP, resulting in an average of 3,544 patients per general practice in the region. Practices are located in both urban and rural areas and include solo practitioners and company practices of up to 5 + GPs per practice [40]. The GPs own the practices and employ other HCPs, e.g., nurses, medical laboratory technicians, and assistants.

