### Outcomes

1) Proportion of patients exceeding the Danish low-risk alcohol consumption limit of ten standard units per week and a maximum of four standard units on a single day for men and women.

2) The likelihood of alcohol use being addressed during a consultation in general practice.

3) Number of heavy drinking days (> 4 standard units on one day for men and women) per week among patients in the participating practices.

4) The use of the biomarkers Alanine Transaminase (ALAT) and Gamma-Glutamyl Transferase (GGT) in general practice.

5) Prescribed pharmacological treatment rate of Disulfiram, Naltrexone, Acamprosate and Nalmefene in general practice.

Table 1 presents an overview of study objectives, hypotheses, outcome measures, data sources, and data collection timepoints.

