iii) To evaluate the 15-method’s effectiveness in lowering the number of heavy drinking days per week in patients.	The number of heavy drinking days will decrease in the patient population.	Number of heavy drinking days (> 4 standard units on one day for men and women) per week in patients.	Questionnaires to all patients 18 + years affiliated with participating practices including the AUDIT-C, and TLFB one week version.	Four times during trial. Illustrated in Fig. 2.
iv) Evaluate the frequency of use of biomarkers as a screening tool for harmful alcohol use.	The use of biomarkers as a screening tool for harmful alcohol use will increase.	The use of the biomarkers ALAT and GGT.	The Danish National Laboratory Database.	End of follow-up period.
v) Evaluate the prescription rate of pharmacological treatment for alcohol problems.	Prescriptions of pharmacological treatment for alcohol problems will increase, as the HCPs become more aware of use cases and more familiar with treatment options through academic detailing.	Prescription rate of Disulfiram, Naltrexone, Acamprosate and Nalmefene.	The Danish National Prescription Registry.	End of follow-up period.

*Notes* One standard unit defined as 12 g of ethanol; AUDIT-C, Alcohol Use Disorder Identification Test Consumption; TLFB, Timeline Follow Back; EQ-5D, European Quality of Life 5 Dimensions; WHO-5, World Health Organization Five Well Being Index; ICPC-2, International Classification of Primary Care 2; ICD-10, International Classification of Disease tenth revision; code A97, no disease; code z006, Encounter for examination for normal comparison and control in clinical research program; ALAT, Alanine Transaminase; GGT, Gamma-Glutamyl Transferase; HCP, health care professional

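### Linear regression weighted by practice size and staff numbers is a poor fit for prescriptions and biomarker tests: it costs power on rates, and can inflate type I error if raw counts or the staff weight are used

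*Protocol article*

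**What the plan says.** The Quantitative analyses section of the protocol article fixes the model: "Continuous outcomes, e.g., number of heavy drinking days, the use of biomarkers, and pharmacological prescription frequency will be analyzed using mixed model linear regression". The same paragraph fixes the unit and the weights for every outcome: "Outcomes will be analyzed on practice level with weighted observations according to patient population size and number of participating HCPs in the practice". It does not say how the two weights combine.

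The scale of the two registry outcomes is described unevenly.

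- **Prescriptions.** The Outcomes section has "Prescribed pharmacological treatment rate of Disulfiram, Naltrexone, Acamprosate and Nalmefene in general practice" and Table 1 has "Prescription rate of Disulfiram, Naltrexone, Acamprosate and Nalmefene". The abstract also speaks of a rate. No denominator is given, and the analysis section says *frequency* instead.
- **Biomarkers.** Table 1 has only "The use of the biomarkers ALAT and GGT". Neither a count nor a rate is specified.
- **Data.** The section on pharmacological treatment and biomarkers says "Data will be collected on practice level".

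The trial is planned with 16 practices in four steps of four. The Study setting section describes practices from solo to five or more GPs.

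**The concern.** Numbers of prescriptions and tests per practice and period are event counts. The variance of a count rises with the number of patients at risk, and the variance of a rate falls with it. A linear model weighted by list size assumes that variance falls in proportion to list size. That is correct for a rate and the wrong way round for a count. On counts, the noisiest practices would get the most weight, and the additive effect would mean something different in a solo practice and in a five-GP practice.

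The staff weight is a separate difficulty. The number of participating staff does not measure the precision of a per-patient rate. The Eligibility section also lets each practice decide how many staff take part.

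Table 1 states a directional hypothesis for each outcome. At stake are the error rate and power of those two tests, and whether the estimate has a common meaning across practices.

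**Working it through.** **The plan's own figures.** The article gives no event rate, power or error rate for prescriptions or biomarkers. Its stated power concerns the questionnaire outcome. A stepped-wedge variance formula with four surveys, ICC 0.068 and a one-sided 2.5% level, with survey timing assumed, gives 0.90–0.92 at 50% response and 0.80–0.82 at 37%. These agree with the stated >90% and 81%, but do not bear on this point.

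**Inputs from the article.** The design has 16 practices: "resulting in a total of 16 general practices being randomized to the 15-method in four steps of four practices (clusters". Practice size is "an average of 2.3 GPs and 1,541 patients per GP", so 2.3 × 1,541 ≈ 3,544 patients. With the sample-size inputs, adults per practice are 1,538 × 2.3 × 0.89 ≈ 3,148.

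**Assumed, because the article is silent.**

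- Six quarters and no true effect.
- 1.6 to 120 events per practice-quarter. For rare prescriptions, 1.6 / 3,148 ≈ 0.5 per 1,000 adults.
- Log-normal practice sizes with log-SD *s* of 0.3 or 0.5.
- Staff numbers roughly proportional to list size, with the two weights multiplied.
- Tests at a two-sided 5%.

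**Direction and rough size.** Let *N* be list size, *w* the weight and *v* the true residual variance. If the design contributes equally across practices, the true variance of a weighted estimate exceeds the model-based variance by about

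R = E[w²v] / (E[w] · E[wv]).

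For log-normal sizes with median 1, E[N^k] = exp(k²s²/2). The rejection rate under no effect is then 2Φ(−1.96/√R).

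- Rate, list-size weight (w = N, v ∝ 1/N): R = 1, so 5%.
- Rate, list × staff (w = N², v ∝ 1/N): R = E[N³]/(E[N²]E[N]) = exp(2s²).
- Count, list-size weight (w = N, v ∝ N): R = E[N³]/(E[N]E[N²]) = exp(2s²).
- Count, list × staff (w = N², v ∝ N): R = E[N⁵]/(E[N²]E[N³]) = exp(6s²).

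At s = 0.3, exp(2s²) = 1.20 gives 7.3% and exp(6s²) = 1.72 gives 13.5%. At s = 0.5, 1.65 gives 12.7% and 4.48 gives 35%. The last figure overstates what 16 practices produce, because so small a sample rarely realises the upper tail of the size distribution.

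**Simulation.** Practice and period effects, model-based standard errors, 1,500 trials per cell:

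| Scale and weights | s = 0.3 | s = 0.5 |
|---|---|---|
| Rate, list size | 4.7–6.3% (both spreads) | 4.7–6.3% (both spreads) |
| Rate, list × staff | 7.7–9.3% | 10.7–12.3% |
| Count, list size | 6.1–7.0% | 9.8–12.7% |
| Count, list × staff | 11.7–13.1% | 19.6–22.2% |

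Further runs of the rate model with both weights reached 15% at s = 0.5.

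**Mixed model.** A REML model with a random practice intercept was run with list-size weights only.

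- Counts, equal sizes: 5.9–6.4%.
- Counts, size CV 0.3: 7.6–8.0%.
- Counts, size CV about 0.6: 9.4–13.6% for prescriptions and 10.9–13.7% for biomarkers. One biomarker scenario with a steep period trend gave 3.5%.
- Rates, size CV about 0.6: 5.1–6.8% for prescriptions and 2.4–8.5% for biomarkers.
- Unweighted counts, size CV about 0.6: 3.5–7.0% for prescriptions and 0.6–5.3% for biomarkers. Linear regression by itself is therefore not what inflates the error.

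**Count model with log list-size offset.** Quasi-Poisson gave about 5–6% for rare prescriptions and 7.5–9.5% for high-volume biomarker counts.

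**Power on the rate reading.** At a rate ratio of 2 and 1.6 events per practice-quarter, weighted linear rates gave 65–68% and the count model 75–77%. In another simulation with the same mean count the figures were 67% and 72%.

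**The case against.** The strongest reply is that the article defines prescriptions as a rate in the abstract, the Outcomes section and Table 1, and never calls either outcome a count. Weighting by list size suits a rate, and on that reading the error for prescriptions is about nominal. This stands. A reader might infer that the plan as written doubles the false-positive rate. The documents do not support that, because it requires raw counts or a multiplied staff weight, together with widely varying practice sizes.

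A missing denominator or offset is also the kind of detail that a condensed article leaves to the analysis plan. That stands too, so the omission itself is not the point. What remains is stated text: the continuous label, the linear model and the staff weight. The rate reading does not remove the staff weight.

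A reader might extend the criticism to heavy drinking days, which the same sentence names. That does not follow. At practice level each value is a mean over many respondents, about 3,148 × 0.30 ≈ 944 to 3,148 × 0.50 ≈ 1,574 per survey, and a linear model suits such means.

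Finally, a simple count model is no cure for biomarkers, where quasi-Poisson itself ran above nominal. This is correct and shapes the fix.

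**Conclusion.** The concern holds in a limited form and is minor. For prescriptions analysed as rates with list-size weights alone, the error is sound and the cost is power: about 8 to 10 points in one set of simulations and 5 in another, under assumed rare-event rates. If raw counts are modelled, or the staff weight is multiplied in, the type I error can reach about twice nominal or more when sizes vary widely. It is roughly 6–9% at moderate spread with one of these departures, and near nominal for counts when sizes are equal.

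These sizes rest on assumed event rates, an assumed practice-size distribution, staff numbers proportional to list size and multiplication of the two weights. Other ways of combining the weights could give other results, and robust standard errors were not examined. For biomarkers the scale is open in the article and the results are less clear-cut. Outcomes 4 and 5 are not among the two objectives for which power was calculated, so the main conclusions of the trial are not affected.

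**What to change.** Analyse prescriptions and biomarker tests with a negative binomial, or over-dispersed Poisson, mixed model. Use log(adults on the list × time) as offset, with period effects and random practice effects. Apply no additional size or staff weights, and report rate ratios. For biomarker tests, model the over-dispersion explicitly and check the error rate at realistic volumes before the model is fixed.

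If linear regression is kept, state that both outcomes are rates, name the denominator, weight by list size only and drop the staff weight. The linear analysis of heavy drinking days can stay.

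The cost is analysis-plan wording only. Table 1 places collection of both registry outcomes at the end of follow-up, and the data sources do not change.
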